### 3.10 Demographics

The following demographic parameters are registered for each patient: sex, age, weight, height, BP, heart rate, eGFR, renal diagnosis, other diagnoses, medication, actual and former tobacco and alcohol use, previous CV events. A case report form (CRF) will be filled out for each patient. Laboratory results will be on printed laboratory forms and will be entered into a database from these. Data will be entered continuously.

### 3.11 Laboratory data

| ***Visit number*** | ***Time with reference to randomization for the individual patient*** | ***Blood tests*** | ***Other*** |
| --- | --- | --- | --- |
|  | Screening | b-haemoglobin, b-leukocytes, b-thrombocytes, p-bilirubin, p-ALAT, p-alkaline phosphatase, hsC-reactive protein, p-creatinine, p-urea, p-sodium, p-potassium, p-bicarbonate, p-glucose, p-albumin, p-calcium-ion, p-phosphate, p-uric acid, eGFR, p-cholesterol, p-triglyceride, p-HDL, P-LDL, p-parathyroid hormone (PTH) and 1,25-dihydroxy-cholecalciferol (vitamin D3), 25-OH-Vitamin D, p-renin og p-aldosterone.  p-HCG in fertile women. | ECG |
| 1a | Week 1 | b-haemoglobin, b-leukocytes, b-thrombocytes, p-bilirubin, p-ALAT, p-alkaline phosphatase, hsC-reactive protein, p-creatinine, p-urea, p-sodium, p-potassium, p-bicarbonate, p-glucose, p-albumin, p-calcium-ion, p-phosphate, p-uric acid, eGFR, p-cholesterol, p-triglyceride, p-HDL, P-LDL, p-PTH. | 24 hour urine sampling |
| 1b | Week 1 | return of AMBP device |  |
| 2 | Week 2 | b-haemoglobin, b-leukocytes, b-thrombocytes, p-bilirubin, p-ALAT, p-alkaline phosphatase, hsC-reactive protein, p-creatinine, p-urea, p-sodium, p-potassium, p-bicarbonate, p-glucose, p-albumin, p-calcium-ion, p-phosphate, p-uric acid, eGFR. |  |
| 3 | Week 4 | b-haemoglobin, b-leukocytes, b-thrombocytes, p-bilirubin, p-ALAT, p-alkaline phosphatase, hsC-reactive protein, p-creatinine, p-urea, p-sodium, p-potassium, p-bicarbonate, p-glucose, p-albumin, p-calcium-ion, p-phosphate, p-uric acid, eGFR |  |
| 4 | Week 8 | b-haemoglobin, b-leukocytes, b-thrombocytes, p-bilirubin, p-ALAT, p-alkaline phosphatase, hsC-reactive protein, p-creatinine, p-urea, p-sodium, p-potassium, p-bicarbonate, p-glucose, p-albumin, p-calcium-ion, p-phosphate, p-uric acid, eGFR. |  |
| 5a | Week 12 | b-haemoglobin, b-leukocytes, b-thrombocytes, p-bilirubin, p-ALAT, p-alkaline phosphatase, hsC-reactive protein, p-creatinine, p-urea, p-sodium, p-potassium, p-bicarbonate, p-glucose, p-albumin, p-calcium-ion, p-phosphate, p-uric acid, eGFR, p-cholesterol, p-triglyceride, p-HDL, P-LDL, p-PTH. | 24 hour urine sampling |
| 5b | Week 12 | return of AMBP device |  |
| 6 | Week 16 | b-haemoglobin, b-leukocytes, b-thrombocytes, p-bilirubin, p-ALAT, p-alkaline phosphatase, hsC-reactive protein, p-creatinine, p-urea, p-sodium, p-potassium, p-bicarbonate, p-glucose, p-albumin, p-calcium-ion, p-phosphate, p-uric acid, eGFR. |  |
| 7 | Week 20 | b-haemoglobin, b-leukocytes, b-thrombocytes, p-bilirubin, p-ALAT, p-alkaline phosphatase, hsC-reactive protein, p-creatinine, p-urea, p-sodium, p-potassium, p-bicarbonate, p-glucose, p-albumin, p-calcium-ion, p-phosphate, p-uric acid, eGFR. |  |
| 8a | Week 24 | b-haemoglobin, b-leukocytes, b-thrombocytes, p-bilirubin, p-ALAT, p-alkaline phosphatase, hsC-reactive protein, p-creatinine, p-urea, p-sodium, p-potassium, p-bicarbonate, p-glucose, p-albumin, p-calcium-ion, p-phosphate, p-uric acid, eGFR, p-cholesterol, p-triglyceride, p-HDL, P-LDL, p-parathyroid hormone (PTH) and 1,25-dihydroxy-cholecalciferol (vitamin D3), 25-OH-Vitamin D, p-renin og p-aldosterone. | 24 hour urine sampling |
| 8b | Week 24 | return of AMBP device |  |

Study participants are to collect 24 hour urine samples for analysis of concentrations and total amounts of albumin, creatinine, potassium, sodium and calculation of creatinine clearance at all three visits where pulse wave measurements are made (visits 1, 5a and 8a).

Estimated GFR (eGFR) is routinely performed using the CKD-EPI formula (51).

Re blood samples: At all samplings an amount of blood between 50 and 68 ml of blood will be drawn, depending on purpose of the visit. Analysis is routinely performed in the hospital central laboratory at Herlev Hospital except vitamin D which is performed by Capio Diagnostik and p-renin and aldosterone, which are analyzed at The Dept. of Clinical Physiology, Glostrup Hospital. Both laboratories are usual collaborators for these tests.

Re urine samples: These will be analyzed as routine tests at the central laboratory in Herlev Hospital.

Re frozen tests: Samples will be saved and frozen for later analysis.

Samples are stored in a locked -80°C freezer, which is connected to an alarm system at Herlev Hospital.

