### 3.2 Design

The study is a prospective, randomized, controlled, parallel group, phase IV study.

| Week number | -4 | 1 | 2 | 4 | 8 | 12 | 16 | 20 | 24 |
| --- | --- | --- | --- | --- | --- | --- | --- | --- | --- |
| Visit number |  | 1a/1b | 2 | 3 | 4 | 5a/5b | 6 | 7 | 8a/8b |

A BP target of 120-130/80-90 is set and investigators will strive to keep this constant in patients throughout their enrolled period. Therefore a run-in period of 4 weeks has been planned. All patients are to continue on their normal medication including blockers of RAS, which most of these patients receive before enrolment. If anti-hypertensive treatment needs to be intensified, this is done by adding beta blocker, calcium antagonist or methyldopa. If BP is lower than target pressure medication will be withdrawn, primarily via reduction in calcium antagonism or beta blockade, while RAS-blockade in the initial form is aimed to be kept as it was.

If study participants fail to tolerate the full dose of eplerenone 50 mg once daily, dose will be reduced to 25 mg once daily. In case of the patients receiving potassium supplements at time of enrolment these will be withdrawn before start of intervention.

Participants are randomized after the run-in period and are given consecutive numbers of identification.

The study plan is identical for the two groups.

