3.5 Randomization

Randomization is done by blocks that are of unknown size to the investigators and sponsor by drawing of sealed, opaque envelopes provided by the GCP-unit of Copenhagen University.

At the time of randomization patients are given consecutive numbers of participation. Randomization will take place after the informed consent forms have been signed and the run-in period has been completed. Numbers will be noted in the participants’ CRF and in the patients’ medical file.

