### 3.8 Exclusion criteria

Patients are ineligible for participation in the study if one of the following conditions is present:

- p-potassium is > 5.0 mM
- allergy to contents
- treated with spironolactone
- treated with potent inhibitors of CYP3A4 (see SPC for details)
- treated with lithium, ciclosporin, tacrolimus, prednisolone, or other immunosuppressing drug
- inborn errors of metabolism (see SPC for details)
- pregnancy or lactation
- fertile woman, not using safe contraception devices
- dementia or other psychiatric disorder, making understanding of the study conditions impossible
- other severe, chronic illness besides CKD, including liver insufficiency, according to investigators’ judgement
- vascular surgery including stenting or graftimplantation on a. brachialis, aorta or the carotid arteries
- systolic BP > 200 mmHg
- immeasurable pulse amplitude

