### 3.13 Practical performance of study

Patients who fulfil the inclusion criteria and who are interested in participating in the study are informed about the study. The written information is handed out and will be thoroughly explained. A form of written informed consent is to be signed by the patient and the informant/investigator. If consent is given, dates for the study days will be given.

Demographic data will be registered.

Randomization: When inclusion criteria are met including the performance of a screening for PW measurements and the run-in period has been completed, patients are randomized to the active treatment arm with eplerenone or the control arm for 24 weeks.

Planning:

A deviation of ± 1 week from the initially planned date for visits is permitted. Collection of 24 hour urine is allowed for at time deviation of ± 3 days with respect to blood sampling. Participants’ visits are planned to be identical in both groups.

Visits are planned as shown below:

| ***Visit number*** | ***Time with reference to inclusion for the individual patient*** | ***Purpose of visit*** | ***Estimated time used for the visit*** |
| --- | --- | --- | --- |
|  | Screening | signing of written informed consent, PW measurement test, ECG, blood sampling, demographic data noted | 1-1½ hours |
| 1a | Week 1 | randomization, PW measurement, AMBP, blood sampling, 24 h urine, study medication handed out | 1 hour |
| 1b | Week 1 | return of AMBP device | 10 minutes |
| 2 | Week 2 | blood sampling, BP, increase in study medication | 30 minutes |
| 3 | Week 4 | blood sampling, BP, study medication handed out | 30 minutes |
| 4 | Week 8 | blood sampling, BP, study medication handed out | 30 minutes |
| 5a | Week 12 | PW measurement, AMBP, blood sampling, 24 h urine, study medication handed out | 1 hour |
| 5b | Week 12 | return of AMBP device | 10 minutes |
| 6 | Week 16 | blood sampling, BP, study medication handed out | 30 minutes |
| 7 | Week 20 | blood sampling, BP, study medication handed out | 30 minutes |
| 8a | Week 24 | PW measurement, AMBP, blood sampling, 24 h urine, study medication and packages returned | 1-1½ hours |
| 8b | Week 24 | return of AMBP device | 10 minutes |

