**Before enrolment**

The patient has to sign the forms of consent before the screening procedure is carried out. Screening consists of PW measurement and ECG to confirm sinus rhythm. If laboratory results show 25-OH-Vitamin D < 75 nmol/L this deficiency is treated following the present guidelines (52) for at least 4 weeks prior to randomization and PW measurements. Blood pressure is also evaluated for 4 weeks before start of study treatment. The participant receives a photocopy of the signed inform consent and a calendar with the dates of all visits plotted.

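### The only pregnancy test is at screening, about 4 weeks or more before eplerenone is first handed out, and it is not repeated when exposure begins

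*Protocol*

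**What the plan says.** Section 3.11 of the protocol names the blood tests visit by visit. The screening row ends with "p-HCG in fertile women". The rows for visits 1a, 2, 3, 4, 5a, 6, 7 and 8a do not include it.

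Four weeks lie between screening and treatment. Section 3.2 states: "Therefore a run-in period of 4 weeks has been planned". Section 3.5 adds: "Randomization will take place after the informed consent forms have been signed and the run-in period has been completed". The text headed Before enrolment says the same from the blood pressure side: "Blood pressure is also evaluated for 4 weeks before start of study treatment".

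The visit table in section 3.13 gives the purpose of visit 1a as "randomization, PW measurement, AMBP, blood sampling, 24 h urine, study medication handed out". Randomisation and first dispensing therefore fall on the same visit. That section also allows some slack: "A deviation of ± 1 week from the initially planned date for visits is permitted".

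On eligibility, section 3.8 excludes "pregnancy or lactation" and also "fertile woman, not using safe contraception devices". Section 3.9 lists pregnancy as a ground for withdrawal.

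**The concern.** The protocol treats pregnancy as a bar to entry and considers it worth a blood test, but places that test before a month in which no study drug is given. A woman who conceives during the run-in, or whose pregnancy was too early to show at screening, can be randomised to eplerenone and take her first tablet with no test to reveal it. No later test is scheduled either, so the withdrawal criterion depends on the pregnancy coming to light by other means.

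At stake is an avoidable exposure of someone the protocol itself excludes. Estimation of the effect on pulse wave velocity is not in question.

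**Working it through.** The protocol states no figure on this point that could be reproduced. The check is a reading of the schedule, followed by a rough count of how often a second test would matter.

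**Schedule**

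- p-HCG at screening (3.11): listed.
- p-HCG at visit 1a (3.11): not listed; that panel ends with lipids and parathyroid hormone.
- p-HCG at any of the eight blood-sampling visits from 1a to 8a (3.11): 0 of 8.
- First eplerenone (3.13): handed out at visit 1a.
- Comparison: p-potassium above 5.0 mM is also a laboratory exclusion (3.8), and potassium is measured again at visit 1a (3.11). Pregnancy is not.

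**Age of the test at first dose**

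- As planned: 4 weeks of run-in, so about 4 weeks.
- With the permitted deviation: 4 + 1 = 5 weeks.
- It may be longer if a low 25-OH-vitamin D at screening is treated for more than the minimum of 4 weeks before randomisation. The protocol sets no upper limit, so this is not counted below.

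**Expected yield of a second test**

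Moving the last test 4 to 5 weeks later moves the window of detectable conceptions by the same amount, whatever the assay's early blind period. So:

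expected pregnancies caught = (fertile women given eplerenone) × (annual pregnancy rate) × (weeks gained / 52).

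Inputs:

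- Eplerenone arm: 40 patients (Statistics section).
- Share who are fertile women: not given. Assumed 5% to 15%, so 0.05 × 40 = 2 to 0.15 × 40 = 6 women.
- Annual pregnancy rate under contraception: not given. Assumed 0.5% to 10%.
- Weeks gained: 4 to 5, from the schedule.

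Results:

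- Low: 2 × 0.005 × 4/52 = 0.0008.
- Middle (10% of 40 = 4 women, 1% per year, 4 weeks): 4 × 0.01 × 4/52 = 0.003.
- High: 6 × 0.10 × 5/52 = 0.058.

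The range corresponds to one pregnancy caught per 1/0.058 ≈ 17 trials of this size at the high end, and one per 52/(2 × 0.005 × 4) = 1,300 at the low end. Only the eplerenone arm is counted, because the controls stay on their usual therapy.

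**The case against.** The best defence is that the protocol has a coherent layered plan: a test at screening, exclusion of pregnancy, exclusion of fertile women without safe contraception, and withdrawal if pregnancy occurs. Nothing in it calls for a repeat test, so nothing is contradicted. A pregnancy known or suspected at visit 1a would still bar entry, because the exclusion criteria are not tied to the screening day.

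The expected yield is also tiny and rests wholly on assumptions. The high figure combines the largest share of fertile women, the full extra week for all of them, and a 10% annual rate among women admitted only if they use safe contraception. The protocol describes no specific pregnancy risk for eplerenone, and the product summary it refers to is not available here.

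Most of this stands as an argument about priority. The event is rare, the middle estimate of 0.003 is more realistic than the high one, and the size of the harm cannot be taken from the document. The argument does not remove the gap. Contraception at entry and the exclusion wording confirm nothing on the day of first dose, and the sponsor did not rely on contraception alone at screening.

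A smaller objection is that holding the first tablet until visit 1b would treat these women slightly differently around the baseline ambulatory recording. It does no real harm, because it only keeps their baseline recording free of drug.

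**Conclusion.** The concern holds. As written, a fertile woman can start eplerenone on the strength of a pregnancy test about 4 weeks old, or 5 with the permitted deviation, with no test at first dose or later.

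This is a participant-safety matter for an assumed 2 to 6 women, with an expected yield of roughly 0.001 to 0.06 pregnancies caught. The length of the gap comes from the protocol; the number of women and the pregnancy rates are assumptions. The sample size, the primary endpoint and its analysis are untouched. The case for changing the schedule rests on its very low cost set against an exposure that the protocol means to prevent.

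**What to change.** In section 3.11, add p-HCG for fertile women to the visit 1a row, or allow it on a sample taken shortly before that visit. State that a negative result must be seen before the first tablet is taken. Preferably it is read before the randomisation envelope is drawn: withdrawn patients are not replaced, so a positive result found afterwards costs one randomised patient.

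If the result is not ready on the day, the first tablet can wait until visit 1b, when the ambulatory blood pressure device is returned.

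The cost is one assay per fertile woman, on blood already drawn if visit 1a is used, with no extra visit or venepuncture in that case, and possibly a short wait before the first dose. Further p-HCG tests during treatment in fertile women on eplerenone would be optional; the criteria in 3.8 and 3.9 do not require them.

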### 3.12 Study equipment

Devices which will be used in this study are the ambulatory blood pressure measurement device SpaceLabs 90 217 form SpaceLabs Healthcare, Washington, USA.

For pulse wave recordings we use the applanation tonometer (Millar, Houston, Texas, USA) and the SphygmoCor data handling programme from Atcor Medical, Sydney, Australia.

Office blood pressures are measured using a sphygmanometer.

### 3.13 Practical performance of study

Patients who fulfil the inclusion criteria and who are interested in participating in the study are informed about the study. The written information is handed out and will be thoroughly explained. A form of written informed consent is to be signed by the patient and the informant/investigator. If consent is given, dates for the study days will be given.

Demographic data will be registered.

Randomization: When inclusion criteria are met including the performance of a screening for PW measurements and the run-in period has been completed, patients are randomized to the active treatment arm with eplerenone or the control arm for 24 weeks.

Planning:

A deviation of ± 1 week from the initially planned date for visits is permitted. Collection of 24 hour urine is allowed for at time deviation of ± 3 days with respect to blood sampling. Participants’ visits are planned to be identical in both groups.

Visits are planned as shown below:

| ***Visit number*** | ***Time with reference to inclusion for the individual patient*** | ***Purpose of visit*** | ***Estimated time used for the visit*** |
| --- | --- | --- | --- |
|  | Screening | signing of written informed consent, PW measurement test, ECG, blood sampling, demographic data noted | 1-1½ hours |
| 1a | Week 1 | randomization, PW measurement, AMBP, blood sampling, 24 h urine, study medication handed out | 1 hour |
| 1b | Week 1 | return of AMBP device | 10 minutes |
| 2 | Week 2 | blood sampling, BP, increase in study medication | 30 minutes |
| 3 | Week 4 | blood sampling, BP, study medication handed out | 30 minutes |
| 4 | Week 8 | blood sampling, BP, study medication handed out | 30 minutes |
| 5a | Week 12 | PW measurement, AMBP, blood sampling, 24 h urine, study medication handed out | 1 hour |
| 5b | Week 12 | return of AMBP device | 10 minutes |
| 6 | Week 16 | blood sampling, BP, study medication handed out | 30 minutes |
| 7 | Week 20 | blood sampling, BP, study medication handed out | 30 minutes |
| 8a | Week 24 | PW measurement, AMBP, blood sampling, 24 h urine, study medication and packages returned | 1-1½ hours |
| 8b | Week 24 | return of AMBP device | 10 minutes |

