AMBPs are automatically measured blood pressures during ordinary daily activities for a time period of approximately 24 hours. AMBP has been found reproducible in population studies (25-30), hypertensive populations (46) and diabetics (47). The reproducibility of AASI has been proven less reliable in an essentially hypertensive population (48) . The brachial BP is measured in the office using the ABPM equipment on the non-dominant arm. After manual measurements the apparatus will automatically measure the BP every 15 minutes in daytime, which is defined from 7 am until 11 pm. Hereafter the measurements will be performed every 30 minutes from 11 pm till 7 am (49). All patients receive a diary in which they are to make notes of physical activity, meals and rest as well as bedtime and rising time in the morning. For calculation of AASI a minimum of 21 readings of BP is required. These must be spread out over the whole period with at least 7 successful readings during night time. AASI is calculated in the following manner: (1-(the slope of diastolic BP/slope of systolic BP)). It follows that the stiffer the arterial tree, the more the regression line will go towards 0 and AASI thus towards 1. Previous studies have provided references for AASI in the background population. AASI for normotensive individuals is 0.57. In younger individuals AASI is 0.53 increasing to 0.72 in the elderly (30).

*Intervention – study medication*

The study medication is eplerenone, a selective aldosterone receptor antagonist. It is an approved drug, which in this study will be used on a non-appraised indication. The Summaries of Product Characteristics (SPC) in Danish will be used as reference document for evaluation of possible side effects and will be accessible at the site of investigation when the study is initiated.

Initial recommended dose is 25 mg once daily. The dose will be increased to 50 mg eplerenone in once daily dosing after 1 week. In this study eplerenone will be added to the study participants’ usual medication. The manufacturing company Pfizer Aps has been informed of the study.

*Control*

The control group will continue their usual medical therapy.

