### 3.9 Withdrawal criteria

Withdrawal form the study can be done if one of the following events occur:

- pregnancy
- other serious illness
- cardiovascular event such as myocardial infarction or stroke
- untreatable severe hyperkalaemia
- persisting increase in p-creatinine above 30% of base line value at first control visit
- unacceptable side effects
- participant’s wish to end participation before time
- doubts about the degree of compliance

Decision about withdrawal can be made by investigators. Patients withdrawn are not replaced in the study. In case of withdrawal, the patient will resume regular controls in outpatient clinics.

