## Ethical considerations

*Consequences and advantages of the study*

The study will not directly implicate changes in the treatment of CKD for the individual patient. For the group of patients who suffer from CKD the study aims to reveal possible effects of treatment with eplerenone on arterial stiffness. The result of this could lead to improvement of the prognosis for the CKD patient and the risk of CV disease and death as well as attenuation of progression of uraemia.

*Draw backs and risks of the study*

1: use of time

2: discomfort of having blood samples drawn

3: inconvenience when collecting urine

4: inconvenience when having AMBP device mounted

5: side effects of study medication, including the risk of hyperkalaemia

Re 1: The time used for the patient is quite a lot, but the many visits secure that it is a safe intervention. This is to insure a detection of hyperkalaemia in good time. The many visits also induce a better compliance.

Re 2: At the times of blood sampling a maximum of 68 ml will be drawn. This is done on the first and last visits only. In the remainder of visits, a max. of 54 ml is drawn. This constitutes no risk for the patient.

Re 3: It can be inconvenient to collect urine more often than in a usual outpatient course.

Re 4: Some patients think it tiresome to wear the AMBP device for 24 hours. It is used as a routine examination modality in daily clinical practice. Rarely there are marks from the cuff in the days after the measurements. There are no risks in connection with this examination.

Re 5: Common side effects from the active study drug are seen in more than 1 % and less than 10 % of patients. These can be nausea, diarrhoea, dizziness, hypotension, reduced kidney function and hyperkalaemia. Reduction in kidney function is reversible. The risk of hyperkalaemia is met by the close monitoring plan as described above. The investigational group has good clinical experience in the use of eplerenone in this type of patients.

According to the SPC the following uncommon side effects have been reported in more than 1‰ and less than 1% of patients:

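### The general ±1-week visit window is loose for the two titration visits: first on-drug potassium as late as day 14 (planned 7), and first potassium on 50 mg as late as 21 days after the step (planned 14)

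*Protocol*

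**What the plan says.** Section 3.4 of the protocol starts eplerenone at 25 mg once daily and then says: "The dose will be increased to 50 mg eplerenone in once daily dosing after 1 week". In the visit table of section 3.13, study drug is first handed out at visit 1a (week 1), which is also the randomization visit. Visit 2 (week 2) is for "blood sampling, BP, increase in study medication". Visit 3 (week 4) is the next blood sample. The laboratory table in section 3.11 includes potassium and creatinine at both visits, and section 3.3 names these two as the safety variables.

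Section 3.13 gives one rule on timing: "A deviation of ± 1 week from the initially planned date for visits is permitted". No visit is exempted, and no other section sets a narrower window for visits 2 and 3.

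The section on ethical considerations explains why there are so many visits: "This is to insure a detection of hyperkalaemia in good time". It adds: "The risk of hyperkalaemia is met by the close monitoring plan as described above".

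**The concern.** A week's tolerance is modest against a four-week gap between visits, but large against the gaps around titration. Here it is as long as the whole starting period on 25 mg, and half of the planned interval from the step to the next potassium.

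These are also the weeks in which exposure changes, in patients who may be vulnerable to a rise in potassium. Participants have an eGFR of 15 to below 60 ml/min/1.73 m² (section 3.7), may enter with potassium up to 5.0 mM (section 3.8) and stay on their RAS blockade (section 3.2). A response triggered by a laboratory value, such as dose reduction or withdrawal, cannot start before blood is drawn, so it moves with the same window. What is at stake is participant safety in the eplerenone arm (40 patients planned), not the estimate of the PWV effect.

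**Working it through.** **Inputs**

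- Visit weeks: 1a = week 1, 2 = week 2, 3 = week 4, 4 = week 8 (sections 3.11 and 3.13).
- Window: ±7 days for every visit (section 3.13).
- Dose step: at visit 2 (section 3.13), after one week on 25 mg (section 3.4). I read one week as a minimum.
- Anchor: visit 1a = day 0 = first dose. The laboratory table is headed "Time with reference to randomization for the individual patient", and randomization takes place at visit 1a.

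**Planned days**, as (week − 1) × 7

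- Visit 2: (2 − 1) × 7 = day 7
- Visit 3: (4 − 1) × 7 = day 21
- Step to next potassium: 21 − 7 = 14 days

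**Permitted days**

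- Visit 2, not before one week: day 7 to 7 + 7 = day 14
- Visit 3: 21 − 7 = day 14 to 21 + 7 = day 28

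**Gap from the step to the first potassium on 50 mg, when only one visit moves**

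| Case | Visit 2 (day) | Visit 3 (day) | Gap (days) |
| --- | --- | --- | --- |
| As planned | 7 | 21 | 14 |
| Visit 2 a week late | 14 | 21 | 7 |
| Visit 3 a week early | 7 | 14 | 7 |
| Visit 3 a week late | 7 | 28 | 21 |

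The gap is therefore 7-21 days. The two longest delays do not add up: with visit 2 on day 14, even a visit 3 on day 28 leaves 28 − 14 = 14 days.

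**Window as a share of the planned interval**

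- Visit 1a to visit 2: 7/7 = 100%
- Visit 2 to visit 3: 7/14 = 50%
- Four-weekly visits: 7/28 = 25%

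**With an illustrative narrower window** (visit 2 at 0 to +2 days, visit 3 at ±2 days)

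- Visit 2 and the step: days 7-9
- Visit 3: 21 − 2 = day 19 to 21 + 2 = day 23
- Gap: 19 − 9 = 10 to 23 − 7 = 16 days

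**The case against.** The best defence is that no standard makes ±1 week too wide. The protocol names no unsafe interval, and its ethics section ties early detection to the number of visits rather than to exact dates. Potassium is drawn at all seven visits after the first dose, whatever the window. Other safeguards remain: potassium supplements are stopped, spironolactone and potent CYP3A4 inhibitors are excluded, the dose can return to 25 mg, and there are withdrawal criteria. All of this stands, and it limits the point to an improvement.

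It also stands that a late visit 2 does less harm than it may seem. The step moves with the visit, so the patient spends up to one more week on 25 mg, not an unmonitored week on 50 mg. The clear delay on the higher dose is a late visit 3, and 21 days is still shorter than the routine four-week spacing. But that spacing belongs to later visits, when the dose is no longer being stepped up.

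The one-week titration time could instead be read as a fixed date that overrides the general window, which would remove the day-14 bound. The text does not say so, and the step is listed as an act of visit 2, which has the window. A late visit 3 would still give 21 days.

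A reader might infer more than the documents support:

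- **That the first potassium on 50 mg could come almost at the moment of the step.** This needs visit 2 a full week late and visit 3 a full week early, so that two visits planned 14 days apart fall on the same day. It is a corner case of the arithmetic and carries no weight here.
- **That the protocol already uses a tighter visit window elsewhere.** It says: "Collection of 24 hour urine is allowed for at time deviation of ± 3 days with respect to blood sampling". That tolerance pairs two specimens; it is not a visit window.
- **That the creatinine withdrawal rule is delayed in the same way.** The criterion is a "persisting increase in p-creatinine above 30% of base line value at first control visit". Taking that visit to be visit 2 is an assumption, and a persisting rise implies more than one value.

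**Conclusion.** The point holds as a cheap safety improvement. The protocol applies its general tolerance unchanged to the two visits that govern titration. The first on-drug potassium may then come on day 14 instead of day 7, on 25 mg. The first potassium on 50 mg may come 21 days after the step instead of 14, and within 7-21 days if only one visit moves. This loosens the safeguard that the protocol itself cites against hyperkalaemia.

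The figures rest on three assumptions: visit 1a is the fixed day 0, the step is made at visit 2, and it is not made before one week. The anchor is not fully settled, because the visit table in section 3.13 counts from inclusion while section 3.11 counts from randomization. The figures are limits of what the text permits on this reading, not expected timings.

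A reader might conclude that the plan is unsafe, or that the window contradicts the ethics section. The documents support neither: no interval is shown to be dangerous, and a loose schedule is still a schedule. The PWV analysis and the sample size are unaffected. Confidence is medium, since how wide is too wide is a clinical judgement.

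**What to change.** In section 3.13, give visits 2 and 3 their own window counted from the first dose, for example 0 to +2 days for visit 2 and ±2 days for visit 3. The step then falls on days 7-9 and the next potassium 10-16 days after it. The exact widths are illustrative and are for the clinical team to set. State there, and align section 3.4, that the step to 50 mg is made only at visit 2 and moves with it. Keep ±1 week for the four-weekly visits.

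This is a change of wording and adds no visit or blood sample. The cost is tighter scheduling of two visits per patient that are already planned.
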